## Abstract

**Aims:**

Research and policy initiatives for type 1 diabetes (T1D) across European countries demonstrate an emergent, critical shift towards universal paediatric screening. National adaptations of screening, however, remain under‐researched. The current study, as part of the EU‐funded EDENT1FI programme, aimed to examine the psychosocial impact and acceptability of screening according to local contexts and regions.

**Methods:**

The EDENT1FI screening research programme includes 27 partners involved in implementing screening across eight European countries—four countries already implementing national or local research screening programmes and four countries that are new adopters. The study consists of four sub‐studies with assessments performed at five timepoints, from screening baseline to insulin‐requiring T1D: (1) we examine the screening‐specific psychological impact on families using a novel questionnaire for parents of screened children; (2) we further measure the psychological wellbeing of parents by administering validated questionnaires; (3) we explore parental acceptability through semi‐structured interviews and (4) we explore professional stakeholder acceptability via semi‐structured interviews. Data analysis will integrate questionnaire responses and thematic analysis for the interviews.

**Results:**

Findings should provide a deeper understanding of the psychosocial aspects of universal paediatric screening measured longitudinally. The experience of implementation context across countries will be harmonised with the attitudes towards and practices of screening to inform best practice for scaling up universal screening.

**Conclusions:**

The study will provide essential insights into how best a general population screening program for T1D can be integrated into existing European health systems.

## BACKGROUND

1

Type 1 diabetes (T1D) is a chronic autoimmune inflammatory condition resulting in loss of insulin secreting beta cells and the need subsequently for lifelong insulin therapy.^1^ Across Europe, 300,000 children and adolescents live with T1D,^2^ with associated annual treatment costs of 30 billion Euros to local healthcare systems. Detecting T1D early, and prior to the need for insulin therapy, has significant advantages including better long‐term glucose control,^3^ time to prepare for insulin therapy,^4^, ^5^ and significantly reduced risk of being diagnosed in a diabetic emergency.^6^, ^7^ T1D can now be detected in the presymptomatic stages through the measurement of islet‐specific autoantibodies (Aab) and oral glucose tolerance testing^8^ thus raising the possibility of general population screening for this condition. Furthermore, guidelines are now available for clinically managing individuals identified at these early stages through periodic medical monitoring, education about symptoms of diabetes and psychosocial support.^8^

Screening studies (Table 1), clinical trials and recent national legislations^9^ endorsed for presymptomatic T1D across European countries suggest an emergent, critical shift in the expert and public discourse towards increased uptake of universal paediatric screening. This shift is underpinned by an increasing prevalence of T1D in children,^10^ introduction of less invasive testing, development of staging for presymptomatic T1D^11^ and the progressive licensing of a new immunoprevention therapy, teplizumab, in the US.^12^

**TABLE 1 dme70297-tbl-0001:** Recent and ongoing European paediatric screening initiatives.

Program title	Study characteristics	Primary location	Web‐link
DiaUnion 1.0, (2.0 underway)	Two‐centre, 4000 children screened for biomarkers for T1D, coeliac disease, autoimmune thyroid disease	Capital Region (Denmark) and Region Skåne (Sweden)	https://diaunion.org/en/research/#DiaUnion_20
ELSA	Multi‐centre, 20,000+ children screened for T1D	West Midlands (United Kingdom)	https://elsadiabetes.nhs.uk
Fr1da	Multi‐centre, 200,000+ children screened for T1D	Bavaria (Germany)	https://www.typ1diabetes‐frueherkennung.de
D1Ce	Multi‐centre, 5363 children screened for T1D and coeliac disease	Four regions: Lombardy, Marche, Campania, Sardinia (Italy)	https://www.iss.it/‐/il‐progetto‐d1ce

The **E**uropean Action for the **D**iagnosis of **E**arly Non‐clinical **T1**D **F**or Disease **I**nterception (EDENT1FI) is composed of 27 partners across 13 countries, including academic, industrial and patient organisations. Tailored to individual country health systems, EDENT1FI aims to establish harmonised screening programmes, assess the impact of screening on diverse populations, refine monitoring protocols, develop innovative therapeutic strategies and disseminate findings to stakeholders. The project comprises six work packages (WPs) (Figure 1).

**FIGURE 1 dme70297-fig-0001:**
[figure not shown]
Flow chart of Work Packages for the EDENT1FI programme. The EDENT1FI programme comprises six work packages (WPs), which (1) establish screening programs across Europe, aligning with international recommendations and leveraging insights from previous studies (‘Screening WP’); (2) examine ethical, psychosocial (including acceptability) and economic impacts of screening (‘Impact WP’); (3) focus on refining monitoring pathways and utilising innovative technologies for early‐stage T1D (‘Monitoring WP’); (4) develop a roadmap for preventive and disease‐modifying approaches, utilising adaptive trial designs (‘Therapies WP’); (5) emphasize effective communication and dissemination strategies (‘Communication WP’) and (6) ensure effective project management and governance (‘Governance WP’).

The protocol for the screening programme (Screening WP1) has been recently published.^13^ The protocol outlined in this current manuscript describes the study aiming to explore the psychosocial impact of general population screening (Impact WP2). This study will be conducted across eight European countries, some of which have established general population screening research programmes (Germany, henceforth called ‘Level 3’ country); some have nascent research programmes (United Kingdom, Denmark, Sweden, henceforth called level ‘2 countries’) and others will be starting their screening programmes as part of the EDENT1FI study (‘Level 1’ countries, Czechia, Italy, Poland, Portugal).

The balance of benefits and risks of population screening has drawn recent attention. Clinical outcomes were most often evidenced with drastic (5–10 times) reduced risk of diabetic ketoacidosis (DKA) at clinical manifestation of the disease for screened children.^7^ From the parents' perspective, some psychological trade‐offs were registered and some of these were related to anxiety and depressive symptoms. In ASK, DiPiS, GPPAD and Fr1da, identifying a child with islet‐specific Aab was associated with higher anxiety compared to having an Aab‐negative child, particularly in mothers. Following screening results notification, the German Fr1da study reported significantly increased median PHQ‐9 score in mothers of children with presymptomatic T1D compared to negative controls.^6^ Similarly, in the US‐based ASK study, anxiety level (SAI) in parents of autoantibody‐positive children rose following screening: 74% experienced SAI above clinical threshold at first follow‐up visit.^14^ Furthermore, anxiety arising from waiting for the onset of symptomatic T1D requiring insulin may lead to overly protective behaviours in parents.^4^, ^6^ In a newborn genetic testing study, increased maternal worry was found if the mother herself had type 1 diabetes.^15^

Conversely, psychosocial benefits relate to families of being aware of future diabetes risk. The TEDDY study, an international surveillance T1D program for genetically predisposed children, established that parents (*n* = 54) who knew of their child's positive Aab status demonstrated a decrease in stress in the first year post‐diagnosis and improved quality of life compared to those (*n* = 54) diagnosed in the community.^16^ This suggests a trend towards waning anxiety with time and possibly related to monitoring and support. However, in ASK, at visit 2–6 months after results notification, despite a significant decrease, 69% of parents reported clinically relevant anxiety.^14^

In terms of uptake, in TEDDY, enrolment was high for first degree relatives (65%) but lower from the general population (39%).^17^ Parents' satisfaction was high.^18^, ^19^, ^20^ Parents perceived benefits to outweigh harms^5^, ^21^ and twelve years after screening, parents perceived no adverse effects.^18^ With regards to (dis)continuation, adherence with the monitoring protocol in TEDDY was high at 62%, with large differences across countries,^22^ while in the longitudinal ABIS study, participation was lower at 43.8% at 5–6 years.^23^

Therefore, there appears to be mixed results around population screening. Since the transient character of parental anxiety was established as ‘fading’ with time emotional response,^16^ new investigations tailored to the emotional states resulting from presymptomatic T1D have been called for.^8^ The psychological status needs to be monitored with tailored measures and longitudinally, particularly for families identified to be at risk from the general population. Importantly, these findings need to be distinguished from pre‐existing anxieties and stress from other life events. There is clear need for improved understanding of professional stakeholders' acceptability. A recent guidance suggested careful implementation: by nominating a champion for the program, building a team to implement screening, motivating other providers to participate, integrating screening into existing workflows and streamlining logistics such as ordering and coding for autoantibody panels^24^; however, before improving feasibility, a better understanding of the professionals' views and readiness is warranted. Further insight into the issues associated with acceptability of national population screening programs in countries where implementation is on the rise is required. Finally, European countries' variation in screening programs should be accounted for: what screening ‘is’ in any one country or region reflects pragmatic realities of implementation as well as public attitudes and acceptability.

## AIMS

2

Our overarching aim is to explore the psychosocial impact and acceptability of general population screening for T1D in a regional and culturally sensitive manner.

Our specific aims are:
Evaluate the psychological impact of paediatric T1D screening through established validated self‐reported questionnaires and through the development of a novel questionnaire.Examine the psychosocial impact and acceptability of screening through qualitative interviews with parents.Explore the experiences, views and acceptability of professional stakeholders regarding screening.

## METHODS

3

### Design

3.1

The three aims will be addressed through four sub‐studies:
developing and validating a novel questionnaire for parentsadministering validated questionnaires and the novel questionnaire to parents across Level 1 countriessemi‐structured interviews with parents of children who have undergone or declined screening in Level 1 countriesqualitative interviews with professional stakeholders in Level 1, 2 and 3 countries.

Sub‐studies 1–2 are illustrated in Figure 2, and Sub‐studies 3–4 are illustrated in Figure 3.

**FIGURE 2 dme70297-fig-0002:**
[figure not shown]
Impact questionnaires for parents of screened children from Level 1 countries: Alignment with WP1 and WP3. *Alignment with WP1*: To ensure a representative sample and mitigate potential biases, all parents/guardians participating in the WP1 screening programme will be offered the three validated questionnaires to complete. This sample will be stratified to reflect the various socio‐demographic characteristics. The questionnaires will be administered at study entry (Timepoint 1—screening baseline) and following the provision of test results (Timepoint 2—result notification). A risk decision tree will be used at T2 for ‘positive/presymptomatic’ result families to elicit parents/guardians who have high scores of anxiety and/or depression, according to the HADS questionnaire. These individuals will be promptly referred to psychological or medical professionals for the provision of psychotherapeutic support. *Alignment with WP3*: All parents/guardians participating in WP3 whose children are identified as having presymptomatic T1D will be invited to complete the three validated questionnaires, including a novel questionnaire, at Timepoints 3 (screening completion), 4 (monitoring at 1 year) and 5 (progressed to insulin treatment).

**FIGURE 3 dme70297-fig-0003:**
[figure not shown]
Acceptability interviews with parents and professional stakeholders: Alignment with WP1 and WP3. *Alignment with WP1*: We will conduct semi‐structured interviews with parents at three timepoints including Timepoint 1 (Screening baseline) —‘Decliners’ parents from Level 1 countries—and Timepoint 3 (Screening completion)—parents of ‘screened’ children from Level 1 countries. We will also conduct structured telephone interviews with professional stakeholders (HCPs) at Timepoint 3 (Screening completion). *Alignment with WP3*: We will carry out semi‐structured interviews with parents of ‘diagnosed’ children at Timepoint 5 (Progressed to insulin treatment). Professional stakeholders from all participating countries will be invited to the ‘final workshop’ at Timepoint 4 (Monitoring at 1 year).

Details of patient recruitment are provided for each of the sub‐studies below. Over and above this, all participants will be offered participation in other trials that become available through the anonymised registry (https://www.helmholtz‐munich.de/en/idf/research‐area/european‐pre‐t1d‐registry), and furthermore they will be alerted to the potential for immunotherapy medication in countries where it is available. They will also be asked if they are happy to be contacted in the future.

### Sub‐study 1. Developing and validating a novel questionnaire for parents (English language‐based)

3.2

This sub‐study aims to develop and validate a novel patient‐reported outcome measure for parents of children participating in a general population T1D screening programme tailored to assess the psychosocial impact of presymptomatic T1D diagnosis. The novel questionnaire assesses positive/negative impact of screening. This questionnaire will be validated in English‐speaking countries (UK, US and Europe). Qualitative and validation analyses underpinning this questionnaire will be published separately.

#### Participants (1)

3.2.1

At least 30 mothers, fathers, parents or guardians (further—‘parents’) of children who screened and tested negative or positive and those considering screening for T1D will be purposively recruited to take part in 1:1 in‐depth or focus group explorative interviews; approximately 250 parents will take part in validation of the survey and 20 parents will participate in cognitive interviews. To be eligible, an individual must meet the following criteria: (a) mother, father, parent or legal guardian of a child who has undergone or considered screening; (b) age of at least 18 years; (c) comprehends written English and (d) understands the study protocol and signs the informed consent document.

#### Data collection (1)

3.2.2

1.1In‐depth interviews will be conducted with eligible participants via video conferencing. The guide will explore anxiety/ distress, acceptance/understanding, behaviour and coping strategies in parent and child, including social implications and the role of the support network. This data will inform the initial development of questionnaire items.1.2Cognitive debriefing interviews will then be completed with eligible participants, eliciting information regarding clarity and rationale of instructions, meaning of individual items, appropriateness of response choices and any overall comments on the relevance and complexity of the questionnaire.1.3Survey of the novel questionnaire will be administered via Qualtrics‐enabled secure link to the participants from a wider population of families considering screening or screened to ensure representation of views.

Participating ‘Level 1’ countries' centres will translate the questionnaire into the relevant languages and ensure its cultural adaptation.

#### Data analysis (1)

3.2.3

1.1Focus group and individual exploratory interview data will be transcribed by a professional transcriber. NVivo will be used to pull together codes and associated quotations. Thematic content analysis^25^ will be deployed. At the completion of qualitative data analyses, all coders and investigators led by the second author (KB) will meet and generate items for the novel measure.1.2Cognitive debriefing data will be analysed as follows: a senior researcher (KB) will listen to all audio‐recorded interviews and summarise into key themes. A summary of the feedback will be created and discussed at length between senior researchers until consensus is reached on questionnaire revisions.1.3Surveys will be imported into the secure REDCap server, with unique study IDs assigned to each participant. Exploratory factor analysis (EFA) with maximum likelihood extraction, direct oblique rotation and pairwise case exclusion in SPSS version 23 will identify the factor structure of the novel measure. The number of factors will be identified using parallel analysis. Associations between demographic variables and the novel measure will be examined, using correlations, one‐way ANOVAs and independent sample *t*‐tests.

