#### Data analysis (2)

3.3.3

Exploratory data analyses and graphical representations of the data will be used to check validity. The study design includes repeated measures on all outcomes; thus, linear mixed‐effect models that correspond well to this structure (e.g. Linear Mixed Models in SPSS) will be used to analyse the data. Subgroup analyses are planned by sex and age (of parents/participant); the main result will be the analyses of the pooled data and a secondary country‐specific analysis (i.e., paired and non‐paired).

Due to the intrinsic nature of the observational study (and not a clinical trial), a randomisation process is not foreseen. However, we are fully aware of the importance of constructing a sample that is representative of the general population. For this reason, we will employ statistical tools capable of addressing potential biases arising from the lack of randomisation. Specifically, multivariate models will be implemented to account for possible confounding variables, such as education level. In addition, a stratified analysis will be conducted, dividing the study population into homogeneous subgroups (strata) based on one or more confounding variables (e.g., age, education level). A dedicated missing data analysis will be conducted to address this issue. Sensitivity analyses will be performed to assess both Missing at Random (MAR) and Informative (Non‐Random) Missingness. Missing data will be evaluated at specific time points as well as longitudinally over time, in order to determine whether dropout has occurred, resulting in loss to follow‐up.

The team identified SAI‐6 as the primary measure, assessing the psychological impact at different time points. The main hypotheses are: (1) in negative families, reduced parents' stress at T2 compared with T1; (2) in positive/presymptomatic families, reduced parents' stress at T4 compared with T2. Additional hypotheses will also be tested. Where patients progress rapidly to insulin after T2, they will only have T2 and T5 responses, but we feel this will be adequate as they would have participated in education. Information on symptom recognition will be given to all participants at the time of education.

The study will be reported according to Consort guidelines.

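### Maximum likelihood factor analysis on a pairwise-exclusion matrix: little harm with sporadic blanks, but possibly unusable if some items apply only to some parents

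*Protocol article*

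**What the plan says.** Section 3.2.3, Data analysis (1), fixes the method for finding the factor structure of the new questionnaire: "maximum likelihood extraction, direct oblique rotation and pairwise case exclusion in SPSS version 23". It adds: "The number of factors will be identified using parallel analysis".

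The sample is given in section 3.2.1: "approximately 250 parents will take part in validation of the survey". Eligibility extends to the "mother, father, parent or legal guardian of a child who has undergone or considered screening". Section 3.2.2 sends the survey to "participants from a wider population of families considering screening or screened to ensure representation of views". Section 3.2 describes the instrument as "tailored to assess the psychosocial impact of presymptomatic T1D diagnosis".

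The article gives no item list, item count, skip pattern, expected item non-response or split of the 250 parents by screening status. Its missing-data plan ("Missing data will be evaluated at specific time points as well as longitudinally over time") stands in section 3.3.3 and belongs to sub-study 2, not to this factor analysis.

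**The concern.** Maximum likelihood extraction treats its input as one correlation matrix from one sample of one size. Pairwise exclusion computes each correlation from whoever answered both items, so two things are no longer guaranteed:

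- **Positive definiteness.** Correlations from different subsets can be mutually incompatible. The matrix then has a zero or negative eigenvalue and the likelihood criterion is undefined.
- **A single N.** The fit statistic and the parallel-analysis reference eigenvalues both depend on N, and here N differs from cell to cell.

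The respondent mix could make this more than a technicality. The instrument is aimed at the impact of a presymptomatic diagnosis, but some respondents will only have considered screening. If some items concern living with a result, those parents may leave them blank, and such blanks follow screening status rather than chance. Correlations among those items would then come from positive families alone, and the remaining correlations from a broader group. At stake are the number of factors and the factor structure of a questionnaire that sub-study 2 uses in four countries.

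**Working it through.** The plan gives no figure of its own for this analysis, so there is nothing to reproduce. The check is a simulation.

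**Criterion.** Maximum likelihood minimises F = ln|Σ| + tr(SΣ⁻¹) − ln|S| − p, where S is the observed correlation matrix of p items. F requires S to be positive definite. A run counts as unusable if the smallest eigenvalue of the pairwise matrix is ≤ 0.

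**Input from the protocol.** 250 parents (section 3.2.1). Everything else below is assumed.

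**Sporadic blanks only**

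- 30 five-point items, 3 factors, loadings 0.65, 300 runs per scenario: 0% unusable at 5% and at 15% random blanks.
- A wider grid (4 factors correlated 0.3; 20, 30 or 40 items; loadings 0.6, 0.8 or 0.9; 300 runs per cell): 0% unusable in every cell up to 10% blanks. At 20% blanks and loading 0.8 the shares were 0%, 0.3% and 11% for 20, 30 and 40 items. At 30% blanks they were 1%, 73% and 100%.
- At 5% blanks and 30 items the expected n per correlation is 250 × 0.95² = 225.6. The smallest seen was about 213, so the single-N problem is slight here.

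**Some items apply to one group only.** Same 30 items: 10 answered by positive families only, 8 by screened families only, and 30 − 10 − 8 = 12 by all, with 5% random blanks on top. The expected n for a pair of positive-only items is (positive families) × 0.95².

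| Considering / negative / positive | Expected n, positive-only pair | Smallest pairwise n seen | Unusable matrices |
|---|---|---|---|
| 60 / 60 / 130 | 117.3 | – | 0% |
| 80 / 100 / 70 | 63.2 | about 57 | 76% |
| 100 / 100 / 50 | 45.1 | about 40 | 100% |
| 100 / 120 / 30 | 27.1 | about 23 | 100% |

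Repeat simulations of this layout gave 70% and 82% with 70 positive families, and 99.7% and 100% with 50.

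**A different layout.** 4 factors, 30% of items answered only by a subgroup, 5% random blanks, 200 runs per cell. Subgroup shares of 10%, 20% and 33% correspond to 25, 50 and about 82 of 250 parents.

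| Items, loading | 10% | 20% | 33% |
|---|---|---|---|
| 20, 0.6 | 100% | 28% | 0% |
| 20, 0.8 | 100% | 94% | 20% |
| 30, 0.6 | 100% | 100% | 27% |
| 30, 0.8 | 100% | 100% | 98% |

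**Parallel analysis.** With a nominal N of 250 on the 3-factor group-specific layout, it returned the wrong number of factors in 17%, 68% and 99% of runs for 70, 50 and 30 positive families. It always returned too many, averaging 3.2, 4.0 and 5.5. With sporadic blanks only it was right in every run.

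**Alternatives.** An EM matrix was non-positive-definite in 0% of runs with 70 and with 50 positive families. With sporadic blanks it was only slightly more accurate than the pairwise matrix. Listwise exclusion is a poor substitute: at 30 items and 5% blanks, 250 × 0.95³⁰ ≈ 54 complete cases remain.

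**The case against.** The strongest reply is that the failure depends on items nobody has seen. The domains listed in section 3.2.2 (distress, understanding, behaviour, coping, social implications, support) can all be put to parents still considering screening. The interviews behind the items include such parents, and cognitive debriefing should expose questions that make no sense to them. If every item applies to everyone, or answers are forced, the group-specific problem disappears. The article is also condensed and defers the validation analyses to a separate publication. A failed matrix would be noticed and could be re-analysed from the same data.

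Most of this stands, and it limits the point to a conditional one. It does not remove it: the combination of maximum likelihood and pairwise exclusion is stated in the text rather than left open, and it has no advantage over the alternatives. A wrong factor count, unlike a failed extraction, could also pass unnoticed.

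Two objections to the remedy are fair. EM and full-information methods do not supply one obvious N for parallel analysis either, so N has to be chosen and stated. Factoring positive-only items in 30 to 70 families will be imprecise.

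**Conclusion.** The stated method is a poor choice with a conditional cost. With random blanks up to about 10–15% in 250 parents the effect is small and no fitting failure was seen. If a substantial block of items applies only to positive or screened families, and positive families number about 30 to 70, the matrix was unusable in about 70–100% of runs under the assumed 30-item layout. With 130 positive families it was 0%. Item count, loadings, group-specific blocks and respondent mix are all assumptions.

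A reader might infer more than the document supports:

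- **That parents considering screening cannot answer some items.** The items are not shown, so this is only possible.
- **That the harm arises whichever parents are surveyed.** The lack of a guarantee is general, but the failure rate depends strongly on the mix and the items.
- **That the analysis must either stop or describe a population that does not exist.** With sporadic random blanks, all pairwise correlations estimate the same population.
- **That the items used in sub-study 2 are selected on this analysis.** Section 3.2.3 derives items from the interviews and revises them after debriefing. The factor analysis is said only to identify structure.

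The point is confined to sub-study 1. SAI-6, the primary measure, and the two main hypotheses in section 3.3.3 are unaffected.

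**What to change.** In section 3.2.3, replace pairwise exclusion with an EM or full-information maximum likelihood covariance matrix, or multiple imputation, for blanks on items that apply to the respondent. Check that the matrix is positive definite before extraction. Run the parallel analysis on the same matrix with one stated N.

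If any items apply to one group only, factor them within that group and treat the result as exploratory where the group is small. An EM matrix would be positive definite even so, but it would fill in answers to questions that have no meaning for the respondent.

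The cost is a sentence or two of wording and slightly more analysis work, with no new data. The downside is imprecise group-specific factoring when few positive families respond.
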